## Abstract

**Background:**

Physical activity is associated with the reduction of several chronic conditions in adults. Additionally, physical activity is extremely important for children for their development and cognitive functioning and also to create a physically active lifestyle that continues into adulthood. Despite the known benefits of physical activity, only one in five adults are achieving the public health recommendations of 150 minutes of moderate-to-vigorous physical activity per week and only 13 % of boys and 6 % of girls between the ages of 5 and 17 years are meeting the guidelines of 60 minutes per day. This study aims to evaluate whether a planning condition improves adherence to regular physical activity compared to an education-only control condition among families. Families are eligible if there is at least one child between the ages of 6 and 12 years who is not meeting the Canadian Physical Activity Guidelines.

**Methods/design:**

A six-month longitudinal randomized controlled trial will be used to compare the two conditions. Materials will be delivered at baseline with ‘booster’ sessions at six weeks and three months. Participants will be assessed at baseline and at six months with a fitness test, as well as questionnaires and accelerometery at baseline, six weeks, three months and six months. A total of 137 families have been recruited thus far from Greater Victoria. This study is ongoing and recruitment will continue until December 2015 with the target goal of reaching 160 families.

**Discussion:**

This protocol describes the implementation of a randomized controlled trial that utilizes planning strategies to try and increase physical activity among families. Research findings could be useful in public health in providing effective strategies to families to help decrease sedentary lifestyles. Additionally, findings may help to inform future interventions aimed at increasing physical activity among families.

**Trial registration:**

This trial was registered on June 5, 2012 with the Clinical Trials Registry maintained by the National Library of Medicine at the National Institutes of Health. The registration ID is NCT01882192.

## Background

Recent reports suggest that sedentary lifestyles are rapidly increasing which pose as a serious risk factor for many adverse health outcomes. Sure enough, the burden of chronic disease is increasing as are obesity rates. According to the most recent data from the World Health Organization and Statistics Canada, the two leading causes of death are from heart disease and cancer with approximately 29.9 % of Canadian adults dying from cancer and 19.7 % from heart disease [1]. Additionally, obesity rates are on the rise. Almost 60 % of Canadians are either overweight or obese, and this has become an ever-increasing trend [2, 3]. This is also the case with children. Approximately one third (31.5 %) of Canadian youth aged 5 to 17 years old are overweight or obese [2, 4]. Obesity is rapidly becoming one of the more serious public health challenges of this century. The need for changes to modifiable risk factors associated with obesity and chronic diseases is paramount.

Physical activity (PA) is associated with the reduction of several chronic diseases in adults, including breast cancer, colorectal cancer, cardiovascular disease (CVD), stroke, high blood pressure, type 2 diabetes, osteoporosis, and hypertension [5]. Furthermore, there is a dose–response relationship between physical activity and these disease states, which means that the more activity performed, the greater the health benefits, such as reducing the risk of premature all-cause mortality [5]. In fact, physically active individuals have an approximate risk reduction of 31 % - 45 % for premature all-cause mortality compared to physically inactive individuals [5]. Physical activity can provide numerous benefits for children as well. In children 5 to 17 years old, physical activity and high physical fitness help guard against high blood pressure, high blood cholesterol, metabolic syndrome, low bone density, depression, injuries, and obesity [6]. Despite these well-known benefits, results from the latest Canadian Health Measures Survey (CHMS) brought to light some alarming statistics. Adults aged 18 to 79 accumulated on average of 12 minutes per day of moderate-to-vigorous physical activity for a total of 84 minutes per week [7]. Current recommended guidelines suggest adults achieve 150 minutes of moderate-to-vigorous physical activity (MVPA) per week working out to about 30 minutes a day five times a week [8]. Only about 1 in every 5 adults are achieving these public health recommendations. Even more alarming were the results for Canadian children showing that for kids between the ages of 5 and 17 only 13 % of boys and 6 % of girls were achieving the guidelines of 60 minutes a day of MVPA [9].

It is widely accepted that children and youth are influenced by the settings they spend their time in and by the adults in those settings. The home is a key environment and parents are the adults that typically govern health promotion choices as children are not cognitively prepared to make decisions that influence long-term health outcomes [10]. There has been significant research on parental correlates of PA among children. For example, in a recent review of reviews by Rhodes and Quinlan [11], they report on over 100 studies that have focused on family influence and child physical activity. Among several types of family correlates (e.g., parental role modeling, parental support, parental attitudes about PA, general parenting styles and overall family cohesion), parental support has the most clear and consistent evidence as a correlate of child PA.

Obviously, regular life-long physical activity is the desired strategy for reducing the risk of chronic diseases and obesity; thus promotion efforts should be targeting families due to the influence parents have on their children’s physical activity levels as well as the decline in PA for parents [11].

### Theoretical framework

Unfortunately, while parental support is a key correlate of child physical activity, few interventions at the family-level have yielded behavior change outcomes [12]. In order for interventions to be effective in changing behavior, it has been suggested that a sound understanding of physical activity determinants, preferably via a theoretical framework is needed [13].

The majority of the interventions that have been conducted involved educational materials on the benefits of child and family physical activity, which may not effectively mediate parental support [12]. For example, Rhodes and colleagues [14] used an adapted theory of planned behavior model [15] to understand parental support of child physical activity and showed that most parents already viewed physical activity as very important for their children. Thus, attitudes about the benefits of child physical activity had no correlation with child physical activity due to this ceiling effect. Conversely, other research by Rhodes et al. [16] showed that parental self-regulation skills – particularly planning, monitoring, and seeking out opportunities for child activity - were critical to child physical activity. Our research complements several researchers/theoreticians who have begun to expand traditional social cognitive theories, focusing on increasing attitudes and control into motivational and volitional planning phases for successful physical activity adherence [17–20].

The Multi-Process Action Control Framework (M-PAC) [19, 21] is more in line with these approaches. In this framework, parents intending to support family physical activity for their children are thought to be influenced by affective attitude (enjoyment of the behavior) and perceived control (ability and opportunity to perform the behavior if desired), and are largely dependent on the higher use and quality of regulation behaviors (e.g., planning, seeking opportunities, self-monitoring). Therefore, the purpose of this paper is to describe the protocol for a family physical activity intervention guided by M-PAC and focused on building high quality planning strategies to create opportunities to enact fun physical activities.

### Pilot research

This research builds on a pilot study conducted from January 2007 until December 2008 in the Capitol Region District of British Columbia that intervened with 85 families [22]. The measures, intervention protocol, recruitment, training of personnel, and related practicalities were all tested during the pilot. The pilot work was successful in demonstrating both sustained recruitment and expected outcomes. As hypothesized, the planning intervention resulted in higher family physical activity compared to the standard condition (effect size η = .08 to .11). Furthermore, the results showed no changes to intention or perceived behavioral control, supporting the concept of a self-regulatory planning phase in physical activity adherence. While these findings were promising, the study was pilot in nature and thus the current trial represents an extension of the work; increasing the methodological veracity and the sophistication of the intervention. First, this study improves upon the pilot study by using direct assessment of physical activity (i.e., accelerometry) rather than self-report, which is the recommended form of assessment for these population groups [23, 24]. Second, this study will evaluate the efficacy of the intervention across six months rather than the one-month time frame used in the pilot. Third, the current study provides a more comprehensive planning skills intervention package based on contemporary theory [20, 21]. Fourth, the study will include health-related assessments of quality of life and physical fitness which were absent in the pilot. These assessments are important markers of health benefits in addition to physical activity and help ascertain whether any changes in behavior actually link to the sought after health improvements that form the central rationale for physical activity promotion.

### Present research

The primary research question is whether a planning condition improves adherence to regular physical activity compared to a control condition at six months. We have four secondary research questions that will also be examined:Does the planning condition improve motivational, health-related quality of life, and health-related fitness outcomes compared to the control condition at six months?Can group differences among these motivational, behavioural, and health-related fitness outcomes be explained through a mediation model?Can motivational variables predict adherence? Do these differ by condition? Our hypothesis is thatIs there an intergenerational, seasonal, or gender difference across primary outcomes by assigned condition?

### Hypotheses

We hypothesize that adherence will be higher for the planning condition in comparison to the more standard physical activity education condition. We also propose that the effect may wane over time from the initial measurement period but all outcomes will remain significantly higher at six months. We hypothesize that the planning condition will not affect intentions but will positively affect health related fitness and QOL. We also hypothesize that the covariance of the assigned conditions (planning, education) on use/adherence will be explained by planning and the use of behavioral regulation strategies (i.e., manipulation check). In turn, the covariance between planning and behavioral regulation strategies and health-related outcomes will be explained by physical activity adherence among conditions. In addition, affective attitude and perceived behavioral control will predict intention, intention will predict planning and planning will predict adherence across conditions. Finally, we hypothesize that children will show greater adherence to the planning condition than their parents. No differences in gender or season are hypothesized but these are exploratory research questions because there is limited research at present to make any definitive statement.

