#### Motivation

Motivations for family based physical activity and personal physical activity will be measured using the constructs of the theory of planned behavior [15] including intention affective attitude, instrumental attitude, perceived control, adapted within the M-PAC framework [21]. Our measures of the theory of planned behaviour are validated from our previous research and have shown excellent predictive validity and internal consistency in adult [14, 16, 34] and child/adolescent [35] populations. These have been validated for both personal and family-based (i.e., activities as a family collective) physical activity [34]. Items will measure all components of the model (affective attitude, instrumental attitude, injunctive norm, descriptive norm, perceived control) including behavioural, normative, and control beliefs developed from prior pilot work in families. There will also be a measurement of habit [36] and identity [37] commensurate with the M-PAC model. The questionnaire will be completed by both parents and the target child. Change in motivation variables will be examined at baseline, six-weeks, three-months and six-months.

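### The hypothesis that planning leaves intention unchanged is matched only with tests of difference, and a non-significant result from these is not evidence of no effect

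*Protocol article*

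**What the plan says.** The Hypotheses section states: "We hypothesize that the planning condition will not affect intentions but will positively affect health related fitness and QOL". The sentence just before it, which follows the prediction on adherence, says that the effect may fade but that "all outcomes will remain significantly higher at six months", and names no exception.

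Intention is a measured secondary outcome. The Motivation section lists the constructs as "including intention affective attitude, instrumental attitude, perceived control, adapted within the M-PAC framework". The first secondary question under Present research is framed as improvement: "Does the planning condition improve motivational, health-related quality of life, and health-related fitness outcomes compared to the control condition at six months".

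The Analysis strategy gives a 2 (condition) x 4 (time) repeated measures ANOVA for the primary question and a variant of it with added factors for the secondary questions. Multilevel methods are added for parent/child clustering. The section on statistical power sizes the trial to detect an effect on adherence.

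The Pilot research section shows how a null result on intention has been read before: "the results showed no changes to intention or perceived behavioral control, supporting the concept of a self-regulatory planning phase in physical activity adherence".

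**The concern.** A prediction of no effect cannot be supported by failing to reject a test of difference. Non-significance may mean that the effect is close to zero, or that the interval is too wide to tell. The stated analyses do not separate the two, and the pilot gives a precedent for taking the first reading.

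At stake is the claim that planning acts after intention has formed and not by raising it. The path hypothesis that "intention will predict planning and planning will predict adherence across conditions" does not settle this, because the chain also fits an intervention that raises intention first. Among the stated hypotheses, the null on intention is the one that directly excludes that rival explanation, so it matters how it is judged.

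**Working it through.** The article states no figure for the intention hypothesis, so there is none to reproduce. Its 160 families are sized for adherence. Only the expected number of completers is taken from that section.

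**Inputs**
- Families per arm: 80; attrition 25% (Statistical power and sample size). Completers per arm: 80 x 0.75 = 60.
- Correlation over time: .75, stated for the adherence outcome. Its use for intention is an assumption, so results are given without adjustment and with adjustment at .75.
- True effects of 0.2 and 0.3 SD: illustrative assumptions; the article gives no effect size for intention.
- One intention score per family at six months, two-sided 5% test, normal approximation.

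**Standard error of the difference, in SD units**
- Unadjusted: sqrt(2/60) = 0.183.
- Baseline-adjusted: 0.183 x sqrt(1 - .75^2) = 0.183 x 0.661 = 0.121.

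**Chance of a non-significant result**, approximately Φ(1.96 - d/SE)

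| True rise d | Unadjusted | Adjusted, r = .75 |
|---|---|---|
| 0.2 SD | Φ(1.96 - 1.10) = 81% | Φ(1.96 - 1.66) = 62% |
| 0.3 SD | Φ(1.96 - 1.64) = 62% | Φ(1.96 - 2.48) = 30% |

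With no attrition (80 per arm), the unadjusted and adjusted figures are 76% and 52% at 0.2 SD, and 52% and 18% at 0.3 SD.

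**What an interval could show with 60 per arm.** The 90% confidence interval half-width is 1.645 x SE: 0.30 SD unadjusted and 0.20 SD adjusted. The power of two one-sided tests at a true difference of zero is 2Φ(margin/SE - 1.645) - 1, taken as zero if negative.

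| Assumed margin | Unadjusted | Adjusted, r = .75 |
|---|---|---|
| 0.2 SD | 0% | 1% |
| 0.3 SD | 0% | 60% |
| 0.4 SD | 42% | 91% |
| 0.5 SD | 73% | 99% |

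Equivalence can be shown with 80% power for a margin of (1.645 + 1.282) x SE, which is 0.53 SD unadjusted and 0.35 SD adjusted.

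**The case against.** The strongest reply is that this is a condensed article. A margin or an interval rule for a secondary outcome may sit in an analysis plan that is not shown, and its absence here is not a fault in itself. That is fair. The point rests instead on what the article does state: a null offered as a hypothesis, difference tests for the secondary questions, and a pilot null counted as support. The pilot sentence describes past results; it sets no rule for this trial. It shows a risk of misreading, not a commitment to it.

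The arithmetic is also simplified. Parents and the target child complete the questionnaire at four time points, and a condition-by-time test uses within-person change, so the unadjusted figures may be too pessimistic. With adjustment at .75, a 0.3 SD rise would be missed in 30% of trials, which is a minority. The worry is strongest for smaller effects or a weaker correlation.

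Some stronger readings do not hold:
- **The whole theory test rests on this null.** It does not. The Hypotheses section also sets mediation and path hypotheses that can be tested positively.
- **The hypothesis cannot be refuted because higher outcomes are predicted throughout.** A significant rise would contradict the specific statement that "the planning condition will not affect intentions". That statement comes directly after the general one and qualifies it. The general sentence is loose wording.
- **The research question contradicts the hypothesis.** It asks and does not predict, and motivation covers more constructs than intention.
- **The design can only fail to find a difference.** The same data can support a claim of equivalence if an interval is judged against a margin set in advance.

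**Conclusion.** The point holds as a cheap improvement to a secondary hypothesis. The article predicts no effect on intention, names only analyses that test for a difference, and cites a pilot in which no change was taken as support. With 60 completers per arm, a non-significant result would be the more likely outcome at a true 0.2 SD rise (62% to 81%). At 0.3 SD it would be common (30% to 62%). The lower end of each range assumes that the .75 correlation given for adherence also applies to intention; the upper end makes no use of it. The effect sizes are illustrative.

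The primary outcome, the sample size and the primary comparison are unaffected.

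**What to change.** 1. In the Hypotheses section, exempt intention explicitly from the statement that "all outcomes will remain significantly higher at six months".
2. Report the baseline-adjusted six-month difference in intention with a 90% confidence interval.
3. Conclude that there is no meaningful effect only if the whole interval lies within an equivalence margin fixed before outcome data are examined. Otherwise report the result as inconclusive and make no claim of absence. If no margin can be agreed, present the estimate and interval alone.

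The cost is a change of wording and one further analysis of data already being collected. The investigators must choose and justify a margin, and power is limited if it is tight: with adjustment at .75 and a true difference of zero, about 60% at 0.3 SD and 91% at 0.4 SD. The Results section reports that 40 families have already completed the study, so the margin should be fixed soon and without sight of outcomes by arm.

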## Methods/design

### Participants and recruitment procedure

Families residing in Victoria, British Columbia with at least one parent and at least one child between the ages of six and 12 years who are not currently meeting physical activity guidelines over the last three months (i.e. parents should accrue at least 150 min of moderate-to-vigorous intensity activity per week (e.g., 5 days x 30 min) and children 60 min of activity daily [8] will be included (screened by self-report through initial recruitment contact interview). We will also conduct a secondary inclusion screen based on baseline accelerometry results which are the golden standard for physical activity assessment [23, 24]. Those families with children who are above the Canadian recommended guidelines that were initially screened into the trial based on self-report will be excluded from the trial. This age group was selected based on earlier pilot work [22] and the fact that children under six years of age engage in physical activity that is extremely sporadic, and thus very different than adults [25]. Our decision to limit the age of children to 12 was based on more pragmatic grounds; in this case, 12 year old children represent the upper bound of the “tweens”, where parents are still very influential in physical activity decisions and planning interventions at the level of the parent would be most effective [10, 12].

### Recruitment

Based on our pilot study recruitment [22], participants will be recruited via advertisements placed in local newspapers, through schools, recreation centres, health care centres, children’s recreation classes, shopping malls, and outdoor markets. In order to ensure diversity in the study population, recruitment is performed by stratifying the city into regions. Within each region, a complete list of schools, recreation centres, health care centres, children’s recreation classes, outdoor markets and shopping malls are obtained and the same number of each type of facility in each region is randomly selected and contacted for recruitment. We currently recruit approximately 5–10 families per week with this strategy. Additionally we incorporated a participant incentive program for snowball recruitment. Any family who refers another family and they enroll in the study is eligible for a $25 grocery store gift card.

### Design

This study is a two-arm parallel design single blinded randomized controlled trial. Participants will be randomised to one of two groups 1) physical activity planning condition; or 2) standard physical activity education condition for six months duration. The RCT has been registered with with the Clinical Trials Registry maintained by the National Library of Medicine at the National Institutes of Health.

### Randomization

Prior to the baseline fitness test, written informed consent will be obtained from the parents, and verbal informed consent will be obtained from the children. A research assistant will explain to the child what is required to participate and the child has to verbally say that they understand and are willing to participate. If a child says no, or remains silent, they will not be eligible to participate in the study. After the baseline fitness test, families (both parents and all children between ages 6–12 years) will be asked to wear accelerometers for one week and will be instructed on how to enter information about each day’s activity into a log. Research assistants will provide a short training session on how to wear and use the accelerometers. After wearing the accelerometer for 7 days, families will be randomized at a 1:1 ratio to either the intervention or control group, using a central computerized system. Participants will be aware of their group allocation, but the fitness testers will be blinded to the treatment allocation. At the end of the week of wear, a research assistant will come to the families’ homes to pick up the accelerometers and go through the study materials and thus the research assistant will not be blind to the families’ condition.

